## Abstract

**Background:**

Parkinson's disease (PD) presents with both motor and non-motor symptoms. Postural and gait aspects, as well as the risk of falls, are important causes of morbidity and mortality in PD. The neural correlates of PD are alterations in the substantia nigra of the midbrain and, among other sites mentioned, the pontine peduncle nucleus stands out. Noninvasive neuromodulation, such as galvanic vestibular stimulation (GVS), can be used in the neural centers involved in motor control alterations in PD. Projections from the vestibular system are involved in motor control and can stimulate the basal nuclei and the pontine peduncle nucleus, as well as strengthen neural networks.

**Objective:**

To analyze the effects of GVS associated with physical-functional exercise on the motor control of PD patients.

**Methods:**

A randomized, placebo-controlled clinical trial. Participants with PD, diagnosed through the Hoehn & Yahr scale (HY) 2 or 3, will be allocated to groups. Pre- and postintervention and follow-up assessments will follow a structured protocol of physical-functional instruments, as recommended in the European Guidelines for managing people with PD. The intervention for both groups will follow the American Neurofunctional Physical Therapy Guideline for managing people with PD.

**Results:**

It is expected that, in the experimental group, the exercises will be associated with active GVS. Finally, a descriptive and statistical analysis must be conducted to verify the effects of GVS.

**Conclusion:**

The study of new devices focusing on motor control in PD is a novel approach and warrants further investigation in the context of vestibular function.

## INTRODUCTION

Parkinson's disease (PD) is a chronic and progressive neurodegenerative disorder characterized clinically by four cardinal signs (tremor, bradykinesia, rigidity, and postural instability) resulting from the progressive loss of neurons in the compact part of the substantia nigra, located in the midbrain.
1

The worldwide prevalence of PD is around 150 to 300 per 1 million inhabitants, and 2 to 3% in individuals over 65-years-old, rising to 4 to 5% in the population over the age of 85 years.
2
A study in the municipality of Bambuí, in the state of Minas Gerais, Brazil, found a prevalence of 3.3% in individuals over 65-years-old.
3

Furthermore, PD triggers motor and non-motor signs/symptoms, and the decline in motor control results from alterations affecting the sensory-motor-cognitive systems.
4
Motor control, which includes postural and gait control, depends on the interaction of the sensory (e.g., somatosensory, visual, and vestibular) systems to maintain semi-static and dynamic postural stability, which are deficient in PD.
5
6

Changes in postural stability in PD have been widely studied, and various aspects of motor control are affected, leading to alterations in the execution of this control.
5
7
8
9
Studies of the kinematics and kinetics of gait and stepping have identified the struggles of PD patients with initiating stepping, demonstrated by anticipatory postural adjustment, hesitation, impairments in the spatiotemporal parameters of gait, and recurrent freezing of gait.
5
8
10
Falls are the most dangerous consequences of body imbalance.
11

Gray and Hildebrand
12
found that 40% of falls in a cohort of 118 PD patients resulted in physical, functional, and psychological impairment. The physical and psychological consequences of falls can lead to hospitalization, wheelchair dependency, and an incapacitating fear of falling, which can initiate a decline in patients' quality of life. It is estimated that people with PD fall frequently, with approximately 60% annually and around 39% recurrently.
13
14
The risk of falls is associated with different components in PD, such as increasing age, hypotension, and depression.
15
16
17
These alterations are essential characteristics of morbidity and mortality in this pathology.

The neural systems involved in postural instability in PD include impaired processing of neural signals in the substantia nigra and basal ganglia.
18
Other brainstem nuclei can contribute to this condition, including the vestibular ones and the pontine peduncle nucleus (PPN).
19
20

Among nonpharmacological treatments, noninvasive neuromodulation is a known tool that can stimulate and modulate neural centers involved in motor control alterations in this condition. For example, stimulation in the primary motor cortex, left dorsolateral frontal cortex, and the supplementary motor area seems to help treat gait in people with PD.
21
22
23

The vestibular apparatus is a sensory system that complements the corticospinal system,
24
and current scientific studies have proven its involvement in PD.
25
26
Noninvasive neuromodulation can stimulate the vestibular system through the use of galvanic vestibular stimulation (GVS),
27
which has been shown to modulate the production of neurotransmitters (dopamine, noradrenaline, and Gaba) in the circuits of the basal ganglia in animal studies.
18
28
29
Studies have identified that vestibular projections can stimulate the basal ganglia and the PPN, strengthening the neural networks involved in motor control. This may represent a gain in postural stability and a reduction in bradykinesia in PD patients.

Given this, it seems possible that vestibular signals integrate with other sensorimotor inputs in the striatum. This is the central area of vestibular stimuli in the basal ganglia, influencing motor control and clinical implications in treating related disorders.
25

The use of GVS can depolarize vestibular hair cells and first-order neurons, subsequently recruiting the neural pathway and stimulating frontal, temporal, parietal, and cerebellar regions.
27
30
The neural activity generated by GVS recruits the vestibulo-ocular and -spinal reflexes. Consequently, it increases postural stability, as shown in older adults at risk of falling and young people without alterations in body balance, with an improved effect on their postural performance.
31
32
33

Mahmud et al.
1
carried out a systematic review with meta-analysis of the use of GVS in postural balance in people with PD (n = 5) and concluded that it has a positive effect on postural balance. Still, the evidence must be more conclusive because the selected studies show low statistical power, heterogeneous stimulation parameters and methodologies, and a lack of randomization.

About the GVS method applied, the following varied: intensity, from 0 to 0.7 mA; electrodes placed on the mastoids, or on the mastoid and spinous process of the seventh cervical vertebra, or other placements such as mono or bipolar, and biocathode; and duration of stimulation, from 26 seconds to 3 hours. Furthermore, five articles included people with PD in the “on” phase and one article assessed the “on” and “off” phases. The disease's stages ranged from 1 to 4, following the Hoehn and Yahr scale (HY).

The primary limitations observed in the studies that have evaluated the effect of GVS in people with PD are: low number of participants; heterogeneity in clinical pictures (axial symptoms) and disease staging; low statistical power; heterogeneity of GVS parameters and methodologies; and lack of randomization and clinical trial according to the Consolidated Standards of Reporting Trials (CONSORT) guidelines for nonpharmacological interventions.

Additionally, the studies mentioned above did not analyze the effects of GVS associated with physical-functional exercise.
1
27
34
35
Although it has been described that head positioning can interfere with the postural response when a person is standing. Furthermore, the amplitude and direction of head rotation during GVS varies with its positioning, indicating that head movement and posture adopted during the GVS can interfere in the responses.
27

Therefore, the association of physical-functional exercise with GVS should be investigated in patients with PD, since it can potentiate the effects of the latter on motor control. This study has practical and scientific implications and is relevant due to the gaps highlighted in the literature regarding the use of GVS in people with PD and to deepen the knowledge of how this treatment affects motor control in this population. Additionally, the authors propose an innovative non-drug treatment for PD focused on noninvasive neuromodulation techniques that can influence the motor control centers involved in the pathophysiology of PD and minimize fall episodes.

In this context, our principal aim was to analyze the effects of GVS associated with physical-functional exercise on the motor control of PD patients. Our specific objectives were to analyze the effects of this treatment on body balance, gait, postural transfer, manual dexterity, physical capacity, confidence in body balance, risk of falling, and quality of life in patients with PD. Furthermore, we aim to analyze its effects on the safety and satisfaction of patients after treatment, as well as its permanent effects over 1 month.

Our hypotheses are that people with PD undergoing treatment with GVS associated with physical-functional exercise will show better motor control performance than those without GVS (placebo). Furthermore, they will perform better in body balance, gait, postural transfer, manual dexterity, and physical capacity tasks. We also expect an improvement in their quality of life, when compared with the placebo group. We believe GVS associated with physical-functional exercise is safe and satisfactory for PD patients, and that its effects will last approximately 1 month after treatment, with patients maintaining physical-functional exercise.

## METHODS

This study was approved by the Ethical Comitte of the Instituto de Assistência Médica ao Servidor Público Estadual de São Paulo – Hospital do Servidor Público Estadual (IAMSPE-HSPE), under the CAAE number 81822124.0.0000.5463. It was also registered on the Brazilian Clinical Trials Registry (ReBEC) under the number RBR-996f8qn, on February 10, 2025, as well as UTN U1111-1315-4982, on November 6, 2024.

### Study design

The present is a randomized, placebo-controlled clinical trial, which followed the CONSORT guidelines for nonpharmacological interventions.

### Study location

The clinical trials will take place in the Movement Disorder Department at HSPE.

### Inclusion and exclusion criteria

Patients between 50 and 75-years-age, female or male, with a diagnosis of idiopathic PD in stages 2 to 3 of the modified HY, regularly followed up at the Movement Disorder Outpatient Clinic and able to walk independently, will be included presenting in the “on period” and stable on their antiparkinsonian medication for 3 months.

Diagnosis will be based on the Brain Bank for Neurological Diseases criteria at the National Hospital for Neurology and Neurosurgery in London, which requires the presence of bradykinesia and at least one of the three cardinal signs of PD.
36

The exclusion criteria are patients unable to remain independently in the orthostatic position; severe visual impairment or not compensated for with the use of corrective lenses; orthopedic disorders resulting in movement limitations; use of medications affecting the vestibular system (e.g., cinnarizine, flunarizine, betahistine, dimenhydrinate, meclizine and ginkgo biloba, among others); having deep brain stimulation (DBS); a history of seizures, pacemakers, or metallic implants in the head and neck region; and those undergoing neurofunctional physiotherapy who did not agree to suspend this treatment during the study period.

Patients will be assessed in the “on” period, around 40 minutes to 2 hours after levodopa administration. The “on” state standardized for the test is the state in which the patient, according to their point of view, shows the best motor performance and is related to the effect of levodopa.

All patients will be assessed following the Head Impulse, Nystagmus, and Test of Skew (HINTS) evaluation to analyze vestibular function in them.

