### Randomization

People with PD will be randomized according to the randomization website of the University of São Paulo (USP) separating the patients into two groups (Group A: Control, and B: Experimental). The researcher carrying out the interventions and the one in the assessments will stay blind about the randomization (double-blind study).

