### Outcomes measures

The primary outcome (
Table 1
) for this research is body balance, measured through the mini-balance evaluation systems test (Mini-BESTest), as well as the activities-specific balance confidence scale (ABC Scale).

**Table 1 TB250281-1:** Assessment tools for people with Parkinson's disease recommended by the European Physiotherapy Guideline for Parkinson's Disease
39

Outcome	Instrument
Body balance	Mini-BESTest
Locomotion	Spatio-temporal gait parameters, NFoG-Q
Postural transfer	M-PAS
Manual dexterity	Nine Holes and Pins Test
Physical capacity	6MWD with Borg 6-20, FTSTS
Confidence in body balance	ABC Scale
Fall risk	Mini-BESTest
Disease severity	UPDRS
Quality of life	PDQ-39
Safety and satisfaction	Questionnaires on adverse effects and satisfaction

Abbreviations: 6MWD, six-minute walk; ABC, activities-specific balance confidence scale; Borg 6-20, Borg scale 6-20; FTSTS, five times sit to stand; M-PAS, modified Parkinson activity scale; Mini-BESTest, mini-balance evaluation systems test; NFoG-Q, new freezing of gait questionnaire; PDQ-39, Parkinson disease questionary-39; UPDRS, unified Parkinson's disease rating scale (part III – motor).

The secondary outcomes were spatio-temporal gait parameters measured using the BTS G-walk (Kinetec) inertial sensor system. Freezing of gait, measured with the new freezing of gait questionnaire. Postural transfer, measured with the timed up and go test and the modified Parkinson activity scale (M-PAS). Manual dexterity, with the nine holes and pins test. Physical capacity, measured with the six-minute walk (6MW) and five times sit to stand tests. Furthermore, risk of falling was measured through the Mini-BESTest, with a cut-off point of 16.
37
Disease severity was measures through part III (motor) of the Unified Parkinson's disease rating scale (UPDRS). Quality of life was analyzed with the Parkinson disease questionary-39 (PDQ-39).
38
Finally, patients' safety and satisfaction will be determined through a new questionnaire, in which adverse events and participants' satisfaction after treatment will be recorded.

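### With 15 patients per arm and entry across Hoehn and Yahr stages 2 to 3, no stratification by stage is described and the stated analysis has no stage term, so chance stage imbalance costs precision that is cheap to recover

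*Protocol article*

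**What the plan says.** - **Entry (Inclusion and exclusion criteria).** Patients have "idiopathic PD in stages 2 to 3 of the modified HY, regularly followed up at the Movement Disorder Outpatient Clinic and able to walk independently". The section also states "The exclusion criteria are patients unable to remain independently in the orthostatic position", which limits the poor-balance end. No Mini-BESTest score, ABC score or fall history is required. Assessment takes place in the medicated state in which the patient, by their own judgement, "shows the best motor performance and is related to the effect of levodopa".
- **Outcome (Outcomes measures).** The primary outcome is body balance by the Mini-BESTest, together with the ABC Scale. The only Mini-BESTest threshold serves to classify an outcome, not entry: "risk of falling was measured through the Mini-BESTest, with a cut-off point of 16".
- **Allocation (Randomization).** Patients are "randomized according to the randomization website of the University of São Paulo (USP) separating the patients into two groups". No stratification factor or block is described.
- **Size (Sample size calculation).** There are 15 patients per group. No effect size, standard deviation or power is given.
- **Analysis (Statistical analysis).** Groups are compared over time by repeated measures ANOVA at the 5% level, with Friedman's test if the data are not normal. Stage and other covariates are not named.
- **Background (Introduction).** Among the primary limitations of earlier GVS studies the authors name "heterogeneity in clinical pictures (axial symptoms) and disease staging".

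**The concern.** The authors regard differences in stage and axial symptoms as a weakness of earlier work, yet the article describes nothing that handles the stage differences remaining in their own sample, either at allocation or in the model. In a trial of 30, simple randomisation can easily put noticeably more stage 3 patients in one arm.

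If stage affects how much balance changes over the treatment period, two things follow. Stage variation adds noise to the group comparison. And in any single trial with a visible imbalance, readers cannot tell how much of the observed difference to attribute to stage. With no stated power, nothing shows that the trial has precision to spare.

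**Working it through.** **Inputs.** From the article: 15 per arm, two groups, 5% significance level (taken as two-sided). Assumed, because the article does not give them: the share of patients in stage 3, the size of the GVS effect, and how far stage shifts the change in balance. The plan states no figure on this point, so there is none to reproduce first.

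**1. How often the arms differ by chance.** Let X and Y be the numbers of stage 3 patients in the two arms.

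*Binomial model*, X and Y independent Bin(15, p), giving P(|X − Y| ≥ d):

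| p | d = 4 | d = 5 |
|---|---|---|
| 0.5 | 0.200 | 0.099 |
| 0.3 | 0.161 | 0.071 |

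*Fixed-total model*: K of the 30 enrolled patients are stage 3, they are split 15:15, and X is hypergeometric (30, K, 15):

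| K | Difference | Probability |
|---|---|---|
| 15 | 3 or more (9 v 6 or worse) | 0.47 |
| 15 | 5 or more (10 v 5 or worse) | 0.14 |
| 10 or 20 | 4 or more | 0.25 |
| 10 or 20 | 6 or more | 0.05 |

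The difference must have the same parity as K. That is why 3 is a natural step for K = 15 and 4 for K = 10 or 20.

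**2. What an imbalance does to one estimate.** A constant stage difference in balance level cancels in a change over time; only a stage effect on the change itself matters. If stage shifts the change by g SD, an excess of 4 stage 3 patients in one arm moves the group difference by (4/15) × g:
- g = 0.5: 0.13 SD
- g = 1.0: 0.27 SD

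The standard error of the difference is √(2/15) = 0.37 SD. The shift is therefore smaller than the standard error, but not negligible if stage matters a lot.

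**3. What stage costs the unadjusted analysis on average.** With half the patients in stage 3, leaving stage out raises the SD of the change from 1 to √(1 + 0.25 g²). For a true effect of 1.0 SD, the effective standardised difference is 1/√(1 + 0.25 g²):
- g = 0: 1.00, power 0.75
- g = 0.5: 1/√1.0625 = 0.97, power 0.73
- g = 1.0: 1/√1.25 = 0.89, power about 0.65

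With stage balanced by stratification and included in the model, the residual SD returns to 1 on 27 degrees of freedom and power is about 0.75 in all three cases. Simulation agrees. The gain is nil if stage is irrelevant, about 2 to 3 percentage points at g = 0.5, and about 10 at g = 1.0.

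**4. Type I error.** In simulations with no true effect, the unadjusted comparison rejects in about 5% of trials. This holds when stage matters and when scores are cut off at an upper bound.

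**The case against.** **The article is condensed, and its silence is not evidence.** Stratification factors and blocks are often left to the full protocol, and covariates to the analysis plan. This is fair, so the point is that no stratification is described, not that the trial ignores stage. The analysis, however, is stated, and as stated it has only group and time.

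**The design already narrows the range.** The Introduction puts earlier studies at stages 1 to 4. This trial takes 2 to 3 and adds limits on age, medication stability and independent standing and walking. It would be wrong to say that it repeats the earlier heterogeneity; it reduces it and leaves a remainder uncontrolled. Admitting both stages without a balance threshold is also defensible for recruitment and generalisability.

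**Chance imbalance is already covered by the significance level.** This stands. A reader might infer that an excess of stage 3 patients in one arm biases the trial or raises the false-positive rate; the type I error result above shows otherwise.

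**A ceiling is not shown.** A reader might also infer that stage 2 patients, tested in their best state, have little left to gain on the Mini-BESTest, so that the outcome meets a ceiling. The article gives no scale maximum, baseline distribution or expected stage mix, and does not say what separates stage 2 from stage 3. The Introduction describes the systems behind postural stability as deficient in Parkinson's disease generally, with no limit by stage. Any figure for dilution would rest wholly on assumed inputs, and stratifying would not remove it because the same patients are enrolled. None is offered here.

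**Conclusion.** The point holds as a cheap improvement in precision and interpretability. Under the stage mixes assumed above, an arm difference of 4 or more stage 3 patients occurs in roughly 16% to 25% of trials, and a 9 v 6 split or worse in about 47% when exactly half are stage 3. The cost in power depends on how strongly stage affects change, which the article does not tell us. It runs from nothing to about 10 percentage points for a 1.0 SD effect, if stage shifts change by up to 1.0 SD.

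The documents do not support a claim of systematic bias, type I error inflation or a demonstrated ceiling. The abstract's "diagnosed through the Hoehn & Yahr scale (HY) 2 or 3, will be allocated to groups" differs from the 2-to-3 range on the modified scale in the Methods, but this is an editorial matter.

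**What to change.** 1. Keep the entry range. Stratify the randomisation by recorded stage, below 3 versus 3, using small concealed permuted blocks. With blocks of 4, for example, an unfilled block leaves the arms at most 2 apart within a stratum. If the full protocol already stratifies, say so in the article.
2. In the primary Mini-BESTest analysis, include stage and its interaction with time, or use stage and baseline score as covariates. The interaction is needed in the repeated measures form because a stage main effect alone does not touch the group-by-time comparison. Friedman's test has no place for a stage term, so the adjusted model should be named as the primary analysis.
3. Report the baseline Mini-BESTest distribution by arm, so that readers can judge for themselves whether there was room to improve.
4. Use one wording for the stage range in the abstract and the Methods.

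**Cost.** A second randomisation list and one or two degrees of freedom. Stage is already assessed for eligibility, so no new data or patients are needed. Unfilled blocks in two strata may leave the arms slightly off 15:15, and block sizes must be kept from recruiting staff. Should stage prove irrelevant, the loss in power is negligible (0.75 either way).

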### Randomization

People with PD will be randomized according to the randomization website of the University of São Paulo (USP) separating the patients into two groups (Group A: Control, and B: Experimental). The researcher carrying out the interventions and the one in the assessments will stay blind about the randomization (double-blind study).

### Procedures

Figure 1
describes the phases of the study. Participants from both groups will be randomly allocated to the groups. The study will be conducted over 4 to 5 weeks, followed by follow-up.

